## Abstract

**Background:**

Favorable effects of formal pulmonary rehabilitation in selected moderate to severe COPD patients are well established. Few data are available on the effects and costs of integrated disease management (IDM) programs on quality of care and health status of COPD patients in primary care, representing a much larger group of COPD patients. Therefore, the RECODE trial assesses the long-term clinical and cost-effectiveness of IDM in primary care.

**Methods/design:**

RECODE is a cluster randomized trial with two years of follow-up, during which 40 clusters of primary care teams (including 1086 COPD patients) are randomized to IDM or usual care. The intervention started with a 2-day multidisciplinary course in which healthcare providers are trained as a team in essential components of effective COPD IDM in primary care. During the course, the team redesigns the care process and defines responsibilities of different caregivers. They are trained in how to use feedback on process and outcome data to guide implement guideline-driven integrated healthcare. Practice-tailored feedback reports are provided at baseline, and at 6 and 12 months. The team learns the details of an ICT program that supports recording of process and outcome measures. Afterwards, the team designs a time-contingent individual practice plan, agreeing on steps to be taken in order to integrate a COPD IDM program into daily practice. After 6 and 12 months, there is a refresher course for all teams simultaneously to enable them to learn from each other’s experience. Health status of patients at 12 months is the primary outcome, measured by the Clinical COPD Questionnaire (CCQ). Secondary outcomes include effects on quality of care, disease-specific and generic health-related quality of life, COPD exacerbations, dyspnea, costs of healthcare utilization, and productivity loss.

**Discussion:**

This article presents the protocol and baseline results of the RECODE trial. This study will allow to evaluate whether IDM implemented in primary care can positively influence quality of life and quality of care in mild to moderate COPD patients, thereby making the benefits of multidisciplinary rehabilitation applicable to a substantial part of the COPD population.

**Trial registration:**

Netherlands Trial Register (NTR): NTR2268

## Background

Chronic obstructive pulmonary disease (COPD) is a smoking-related pulmonary disorder, characterized by largely irreversible airflow obstruction, multisystemic manifestations and frequent co-morbidities [1]. According to current guidelines, stable COPD is managed with a combination of different treatment components (e.g. smoking cessation, physiotherapeutic reactivation, self-management, optimization of medication adherence) [1], involving different healthcare providers. Currently, treatment is mostly guided by the severity of airflow limitation [2]. However, COPD is a complex disease, with great variation in symptoms, functional limitations and co-morbidities as well as in progression towards more severe stages [3]. Therefore, the existence of several clinically relevant phenotypes calls for a more personalized approach [4]. Ideally, optimal care of COPD patients requires an individualized, patient-centered approach that recognizes and treats all aspects of the disease, addresses the systemic effects and co-morbidities, and integrates medical care among healthcare professionals and across healthcare sectors [5]. Since professional treatment, hospital admissions and loss of work contribute to the economic burden of disease worldwide, there is much interest in systematically improving the quality of care, while reducing total costs for patients with COPD and other chronic illness. Integrated Disease Management (IDM) programs have proliferated as a means of improving the quality and efficiency of care [6].

The most frequently applied IDM programs in COPD patients are pulmonary rehabilitation (PR) programs. According to a Cochrane systematic review, the effectiveness of PR on exercise tolerance and quality of life is well established [7]. In international reports and guidelines, it is acknowledged that PR is indicated for all individuals with COPD who have decreased exercise tolerance, exertional dyspnea or fatigue, and/or impairment of activities of daily living [1,8,9]. However, widespread access is restricted, due to limited availability of resources and high costs [10-12]. Furthermore, PR programs usually include only the more severe patients and last only for a limited period of time [13], while initial benefits seem to decline over time [14-18]. After returning home, patients are frequently insufficiently motivated to continue a more physically active and healthy lifestyle. Unfortunately, general practitioners (GPs) are rarely involved in PR programs and, as a consequence, are often unable to support program methods after a rehabilitation phase has formally been concluded [13].

We previously argued that when components of PR are integrated into a primary care IDM program, patients can be treated in their home environment. Primary care providers can then be (more) involved as direct coaches of this process [19-21]. To establish such a program of combined interventions, the set-up of a multidisciplinary team is vital, in which different healthcare professionals participate and provide their share in the spectrum of the required care (Figure 1). Ideally, patients and healthcare providers are close partners in IDM, in order to better control daily symptoms and promote self-management. Furthermore, strong cooperation between several disciplines in primary care and mutually agreeable collaboration with secondary and tertiary care are prerequisites for integrated chronic care [19].

**Figure 1 F1:**
[figure not shown]
Components of an Integrated Disease Management program for COPD patients in primary care.

Systematic reviews of disease management for COPD patients emphasise the need for well-designed, practical multicenter trials [22,23], including broad representative patient samples [24], with a wide range of physicians and settings to improve external validity [23]. Furthermore, authors of systematic reviews advocate studies designed to evaluate the long-term effectiveness of IDM, [23] and advise more health economic studies across different care settings [24]. When considering the large number of eligible patients for IDM in the community, the potential impact is high. However, no trials have been published that are specifically targeted to measure the cost-effectiveness of IDM in patients recruited in primary care.

Therefore, the aim of the current RECODE (acronym for Randomized Clinical Trial on Effectiveness of integrated COPD management in primary care) cluster randomized clinical trial (NTR 2268) is to assess the cost-effectiveness of an IDM program for COPD patients in primary care in the Netherlands. Based on an earlier controlled clinical trial evaluating the effect of an IDM program in mild to moderate COPD, we found the greatest improvements on quality of life in patients with an MRC dyspnea score >2 [25]. As a result, we based our sample size estimates on the a priori planned subgroup of patients with MRC dyspnea score >2. This article describes the design, rationale and baseline results of this trial.

## Methods/design

### Study objective and design

The RECODE trial is a two-group parallel cluster-randomized clinical trial with a two-year follow-up, conducted in the primary care setting. Our objective is to evaluate the clinical and cost-effectiveness of IDM for COPD patients in primary care. The intervention is delivered by the primary care team, including a GP, practice nurse, physiotherapist and dietician, with a consulting pulmonary physician at hand. To avoid contamination between treatment groups within practices, primary care practices are randomized rather than patients. The Medical Ethics Committee of the Leiden University Medical Centre approved the trial.

## Participants

### GPs

Inclusion of GPs and patients started in September 2010 and was finished in September 2011. Practices were considered as candidates if they were willing to create an integrated COPD management team, in which each member has responsibility for their respective areas of expertise. The practices had to include at least one GP, one practice or extramural respiratory nurse, and one physiotherapist specialized in COPD care. If multiple practices were collaborating (for example with one practice nurse), they formed one cluster which was used for randomization. Our recruitment goal was to enrol representative groups of primary healthcare providers from a broad spectrum of practices in order to enhance external validity. This study was embedded in the Leiden Primary Care Research Network (LEON), which is managed by the department of Public Health and Primary Care of the Leiden University Medical Center. This multi-center research network consists of some 100 general practices in the western region of the Netherlands, in which these practices signed an agreement to collaborate in scientific research.

### Patients

We included all patients who were diagnosed with COPD by their treating physician. We selected patients from electronic medical records (EMRs) of general practices. For all included patients, we attempted to verify the diagnosis by lung function according to the GOLD criteria [1]. If spirometry data were not available, patients were invited to participate for a formal lung function assessment, according to the ATS/ERS guidelines for spirometry [26]. Exclusion criteria consisted of terminally ill patients, dementia or cognitive impairment, inability to fill in Dutch questionnaires, and hard drug or alcohol abusers. We did not exclude patients if a pulmonary physician was considered the main healthcare provider. The GPs checked the selected patients against the formal inclusion and exclusion criteria before the recruitment procedure started. All patients provided written informed consent before participation in the study.

### Intervention

The intervention consists of an IDM program, which is implemented by a multidisciplinary team in general practice. The team consists of at least three members: the GP, the practice nurse, and a cooperating physiotherapist with specific certified training in COPD care. Depending on the team needs, a collaborating pulmonary physician and dietician were added to the intervention team.

We trained the multidisciplinary teams of intervention practices in a two-day course during 2010–2011. During this course, essential components of IDM for effective integrated COPD care in primary care were explained, trained and rehearsed and supervised. Elements of this course are further outlined in Table 1 and included a review of the advice from international guidelines, performing/interpreting spirometry and assessment of disease burden, and motivational interviewing to stimulate a healthier lifestyle including more physical activity and smoking cessation. Furthermore, the healthcare providers were trained in adopting self-management action plans, including early recognition and treatment of exacerbations, encouragement of regular exercise and guideline-based physical reactivation, cooperation and collaboration with secondary care, and instructions in dietician support for nutritionally depleted patients. In addition, they were trained in how to use feedback on process and outcome data to guide and implement guideline-driven integrated healthcare. This continuining medical education course was developed according to recent national and international guidelines [1,27] and was provided by teachers with hands-on experience with the program. At the end of the course, the team designed a time-contingent individual practice plan, agreeing on steps to be taken in order to integrate a COPD IDM program into daily practice. Intervention practices were free in the fulfilment of their individual plans, as long as they were feasible and relevant for the practice. After 6 and 12 months, there was a refresher course for the intervention practices.

**Table 1 T1:** Components of IDM included in the RECODE course for multidisciplinary teams in primary care

**DM interventions**	**Example**
Optimal medication adherence	Tailoring of advices from international guidelines, e.g. frequent exacerbations necessitate inhaled corticosteroids; daily respiratory complaints necessitate long-acting bronchodilators
Proper diagnosis	Performing and interpreting spirometry, assessment of disease burden using MRC and CCQ
Motivational interviewing	Understanding and making use of patients’ personal goal in physical reactivation and lifestyle changes
Smoking cessation counselling	Review of the recent literature, discussion of bottlenecks, applying behavioural techniques and drug therapy for smoking cessation
Applying self-management plans	Teaching self-management techniques, including early recognition and treatment of exacerbations
Guideline based physiotherapeutic reactivation	Using a patients’ personal goal, referral for physiotherapeutic reactivation in patients with MRC score >2.
Dietary interventions	Early recognition and treatment of nutritionally depleted patients

### Web-based disease management application

During the course, the team learned the details of an ICT program that supports recording of process and outcome measures by access to a flexible web-based IDM application, named Zorgdraad (in English ‘Care Ties’). This application combined a patient and a healthcare provider portal. The patient portal provided patients with disease-specific easy written education, and allows personal goals and personal notes. The healthcare portal left space for a protocol for COPD follow-up guidance, quality of life scores, physiotherapy follow-up and examination, smoking cessation, medication records, and facilitates tailored benchmark reports at 6 and 12 months. These reports were generated by the researchers and sent to the practices to support prioritizing the healthcare needs. An experienced instructor provided the practices during the course with all information about Zorgdraad. An account manager supported the practice nurse and GP on individual use of the program in daily practice. It was intended that practice nurses give the COPD patients directions for use on the patient-portal of Zorgdraad.

All practices were in essence free in the usage of Zorgdraad, and in the fulfilment of their plans. Therefore, not all patients received all components of the program, but individual patient-specific care plans are negotiated by the team, in collaboration with the patient. The intensity of the IDM program depended upon the health status and needs of the patient, resulting in some patients receiving all interventions (e.g. smoking cessation, physiotherapy, nutritional support), while stable patients only had regular 6-monthly or 12-monthly follow-up by nurses. Implementation of the intervention was assessed at 24 months (see “Outcomes”).

### Financial coverage of the intervention

We arranged with the local healthcare insurer that all RECODE patients with dyspnea on moderate or worse exertion (indicated by an Medical Research Council (MRC) score of >2) would be totally reimbursed for the intervention, including physiotherapy.

### Usual care group

The control group consists of ‘usual care’ [28], which is based on the 2007 national primary care COPD guidelines [27]. Instead of the multidisciplinary RECODE course, the practice nurse received a course on technical performance of spirometry in primary care only, in order to divert attention from any of the IDM topics mentioned in Table 1. If the results of our study show that the IDM program could substantially improve the health-related quality of life of COPD patients, we will make the entire set of interventions available to the control group after the study has been completed.

## Outcomes

### Time points

We follow patients at baseline, and at 6 and 12 months with a face-to-face interview. Blinded research nurses administer the questionnaires (Table 2) at specific time points. These interviews take place at the general practice or at the patients’ homes, using the web-based application Zorgdraad. At 9, 18 and 24 months we sent questionnaires by post. In addition, retrospectively the researchers extract data from the patients’ EMRs at 24 months over the complete trial period, regarding prescribed medication.

**Table 2 T2:** Overview of measurements per time point in the RECODE study

**Outcomes**	**Baseline**	**6 m**	**9 m**	**12 m**	**18 m**	**24 m**
**Participants**						
Demographic characteristics	X					
Lung function	X					
Co morbidity	X					
CCQ	X	X	X	X	X	X
SGRQ-C	X	X	X	X	X	X
EQ-5D	X	X	X	X	X	X
SF-36	X	X	X	X	X	X
Smoking behavior, guided smoking attempts	X	X	X	X	X	X
IPAQ	X	X	X	X	X	X
SMAS-30	X	X	X	X	X	X
MRC-Dyspnea scale	X	X	X	X	X	X
Exacerbations	X					X
Costs of health care utilization by patients, part A: Health care use Questionnaire, including direct non-medical costs borne by patients/families	X	X	X	X	X	X
Costs of productivity loss: Absence from work Questionnaire	X	X	X	X	X	X
Costs of health care utilization by patients, part B: Data extraction from medical records (health care utilization, medical treatment)						X
PACIC	X	X	X	X	X	X
**Health care providers**						
ACIC	X			X		
Satisfaction, involvement and implementation of the IDM program				X (IG)		
**IDM program information**						
Development costs of the IDM program						X (IG)
Implementation costs of the IDM program						X (IG)
Performance indicators of practices (see Table 4)	X					X

ACIC: Assessment Chronic Illness Care; CCQ: Clinical COPD Questionnaire; EQ-5D: EuroQol-5D; IPAQ: International Physical Activity Questionnaire; MRC: Medical Research Counsil scale; PACIC: Patient Assessment Chronic Illness Care; SF-36: ShortForm-36; SGRQ-C: Saint Georges Respiratory Questionnaire; SMAS-30: Self Management Scale-30.

IG = intervention group only.

Primary endpoint is at 12 months, when we expect to detect the clinically relevant effect of the intervention [20,25]. Total study duration provides 24 months of follow-up, to assess whether benefits can be maintained.

#### Patients

At baseline, we assessed socio-demographic factors (age, gender, socioeconomic status measured through level of education), marital status, lung function and co-morbidity.

### Primary outcome

The primary outcome measure in this study is health status as measured by the Clinical COPD Questionnaire (CCQ) at 12 months. This questionnaire is a disease-specific, 10-item questionnaire that calculates an overall score and three domain scores: symptoms, functional state and emotional state. Patients are required to respond to each item on a 7-point scale with 0 representing the best possible score and 6 representing the worst possible score. This instrument is proven to be sensitive and valid, and easy to administer in primary care. The minimal clinical important difference (MCID) is −0.4 points [29,30].

### Secondary outcomes

Secondary outcome measurements at 6, 9, 12, 18 and 24 months include (the questionnaire for each outcome is provided in brackets):

1. Measures of changes in health-related quality of life (disease-specific as well as generic), measured by :

a. CCQ

b. St. George Respiratory Questionnaire (SGRQ); designed to measure health impairment in patients with asthma and COPD. The first part produces the symptom score and the second part the activity and impact score. A total score can also be calculated. We use a Dutch version of the SGRQ, and consider a −4 unit change as the MCID for within-group comparison [31].

c. The Euro Qol-5D-3L is a generic, preference-based health-related quality of life questionnaire, with many applications in respiratory disease. It consists of 5 dimensions to describe health (mobility, self-care, usual activities, pain/discomfort, and anxiety/depression) each item with three levels of functioning (e.g., no problems, some problems, and extreme problems). We used the value set derived from the Dutch general population that, when applied to the dimensions of the health state, result in a preference-based utility score that typically ranges from states worse than dead (<0) to 1 (full health), anchoring dead at 0. Besides the descriptive system and the off-the-shelf value sets, the EQ-5D includes a visual analog scale (VAS) where an individual rates his own health on a scale from 0 (worse imaginable health) to 100 (best imaginable health) [32,33].

d. Short-Form Health Survey (SF-36) is a 36-item questionnaire that measures two components (physical and mental component). The physical component consists of four domains of health: physical functioning, role limitations due to physical health, bodily pain and general health perceptions. The mental component consists of role limitations due to emotional problems, vitality, social functioning and mental health [34].

2. Measures of change in patients’ lifestyle, illness behavior and knowledge:

a. Smoking behavior, guided smoking attempts;

b. Taking initiatives, investment behavior and level of self-efficacy, as measured by the Self-Management Scale-30 (SMAS-30) [35];

c. Physical activity, as measured by the International Physical Activity Questionnaire (IPAQ) short form. This is an instrument designed primarily for population surveillance of physical activity among adults. The items in this short form are structured to provide separate scores on walking, moderate-intensity and vigorous-intensity activity. The total score is computed by multiplying the duration (in minutes) and frequency (days) of walking, moderate-intensity and vigorous-intensity activities by its energy requirement to yield a score in Metabolic Equivalent Time (MET) minutes.

3. Measures of change in intermediate patient-related outcomes:

a. Dyspnea, measured by the MRC Dyspnoea Scale [36].

b. Exacerbations: moderate (oral prednisone and/or antibiotic courses), severe (hospitalizations). These data were retrospectively extracted from EMRs at 24 months, over the entire follow-up period.

4. Measures of change in healthcare utilization and costs:

a. Development and implementation costs of the program: time and material resources associated with the training of the healthcare providers and the ICT support (measured at 24 months).

b. Costs of healthcare utilization by patients: including all COPD and non-COPD related cost of a) hospitalization, b) medication, c) caregiver contact, and d) revalidation.

Retrospectively we extract data from EMRs at 24 months over the complete trial period, regarding prescribed medication.

c. Direct non-medical costs borne by patients/families, e.g. travel costs. Costs of productivity loss due to absenteeism/presenteeism at work. This was measured at baseline, and at 6, 9, 12, 18 and 24 months.

5. Measures of change in care delivery process: level of care integration according to patients, measured by the Patient Assessment Chronic Illness Care (PACIC) [37]. This questionnaire was self-reported by patients in both groups and was administered at baseline, and at 6, 9, 12, 18 and 24 months.

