### Cost-effectiveness (CEA) and cost-utility analyses (CUA)

The relation between the costs and the estimated health outcomes is expressed in cost-effectiveness ratios: (1) costs per QALY, (2) costs per exacerbation prevented, (3) costs per patient with a clinically relevant improvement of at least 0.4 units on the CCQ, (4) costs per patient with a clinically relevant (4 units) improvement on the SGRQ, and (5) costs per patient with a 1 point improvement on the MRC dyspnea scale. Adopting such a wide range of outcome measures in the economic evaluation is in line with recent guidelines of a joint ATS/ERS task force on outcome measurements in COPD that recommend taking a multi-outcome approach [46]. At the same time, comparison with the cost-effectiveness of other interventions for other diseases is made possible through the calculation of costs per QALY. Uncertainty around cost-effectiveness ratios will be dealt with in probabilistic sensitivity analysis in which costs and health outcomes will be bootstrapped and plotted on cost-effectiveness planes from which cost-effectiveness acceptability curves will be drawn [47-49]. In additional ‘net monetary benefits’ [50] will be calculated using different thresholds of the willingness to pay for a QALY and it will be investigated which patient, practice and team characteristics are related to the size of the net monetary benefits. The economic evaluation will compare differences in costs to differences in effects (CEA) and quality adjusted life-years (CUA). The analysis will have a 12 and 24-months time horizon. Sensitivity analyses will be performed on the perspective (societal versus healthcare) and the applied utility measure (Dutch EQ5D).

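### The moderate exacerbation count is a count of treatment courses, and only the intervention teams are trained in treating exacerbations early, so costs per exacerbation prevented can move without a change in disease

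*Protocol article*

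**What the plan says.** Secondary outcomes, item 3b, of the protocol article grades the events as "Exacerbations: moderate (oral prednisone and/or antibiotic courses), severe (hospitalizations" and adds: "These data were retrospectively extracted from EMRs at 24 months, over the entire follow-up period". The moderate grade is marked by a course of medication, the severe grade by an admission.

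Under Intervention, the providers in that arm were "trained in adopting self-management action plans, including early recognition and treatment of exacerbations". Table 1 lists the matching programme component: "Teaching self-management techniques, including early recognition and treatment of exacerbations".

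The Usual care group section describes care "which is based on the 2007 national primary care COPD guidelines". Practice nurses there received a course on spirometry technique only, "in order to divert attention from any of the IDM topics mentioned in Table 1". The Blinding section states that patients and providers cannot be blinded and that blinded research nurses assess outcomes.

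The section on cost-effectiveness and cost-utility analyses lists five ratios, one of them "2) costs per exacerbation prevented". It does not say whether moderate, severe or both grades make up the denominator.

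**The concern.** An outcome marked by a treatment measures disease only if a given worsening is equally likely to be treated in both arms. Here the programme sets out to change how exacerbations are recognised and treated, and the control training is designed to leave that alone. The arm difference in moderate exacerbations can then combine two things: a change in how often patients worsen, and a change in how often a worsening leads to a course. Blinded interviewers do not help, because the event arises when an unblinded prescriber and patient decide to treat.

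What is at stake is the reading of one secondary outcome and one of the five ratios. The denominator of that ratio is a difference between arms, so a modest shift in treatment behaviour can shrink it, enlarge it, bring it to zero or reverse its sign.

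**Working it through.** The document gives no exacerbation rate, expected effect or treated share, so there is no figure of the plan to reproduce. The check has two parts.

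**The text side by side.** Moderate grade: a prednisone or antibiotic course (Secondary outcomes, 3b). Training in early treatment: given to one arm (Intervention, Table 1) and withheld by design from the other (Usual care group). Prescribers and patients: unblinded (Blinding). Use: the denominator of a cost ratio, grades unspecified. Nothing in the article makes the probability of treatment equal across arms.

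**How far behaviour could move the count.** For the moderate component:

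- observed rate ratio = true rate ratio × (share treated under intervention ÷ share treated under usual care)
- courses prevented per 100 patient-years = 100 × true control rate × (control share − true ratio × intervention share)

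Assumptions, none of them from the document: a true control rate of 1.0 per patient-year (this only scales the counts); 50% of episodes treated with a course under usual care; 45% to 75% under the intervention, as an average over the whole arm.

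| True ratio | Intervention share | Observed ratio | Courses prevented per 100 patient-years | Same, with equal shares |
|---|---|---|---|---|
| 1.00 | 45% | 1.00 × 0.45/0.50 = 0.90 | 5 | 0 |
| 1.00 | 55% | 1.10 | −5 | 0 |
| 1.00 | 60% | 1.20 | −10 | 0 |
| 1.00 | 75% | 1.50 | −25 | 0 |
| 0.80 | 45% | 0.80 × 0.45/0.50 = 0.72 | 14 | 10 |
| 0.80 | 55% | 0.88 | 6 | 10 |
| 0.80 | 60% | 0.96 | 2 | 10 |
| 0.80 | 62.5% | 1.00 | 0 | 10 |
| 0.80 | 75% | 1.20 | −10 | 10 |

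The break-even share for a true 20% reduction is 0.50/0.80 = 0.625.

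The ratio is incremental cost divided by events prevented. With incremental cost held fixed, a denominator of 2 instead of 10 multiplies the ratio by 10/2 = 5. A denominator of 14 instead of 10 multiplies it by 10/14 = 0.71. At 0 the ratio is undefined, and below 0 it changes sign. Adding admissions to the denominator would change these factors, which describe the moderate component alone.

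Early courses that avert admissions would add a further shift, moving events from the severe to the moderate grade. The combined count would hide that shift, whereas the two grades shown separately would reveal it.

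**The case against.** The strongest reply is that the training passages name no drug. That the treatment taught is the treatment counted is an inference, and what the national guideline already offers the control arm on action plans is not stated. This stands, and it is why the point says the count can be biased and not that it is. The inference is still reasonable: the article's own marker of a moderate exacerbation is a course, and one arm is trained to treat exacerbations early.

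Uptake was partial. The section on the web-based application says that not every patient received every component. This reduces any bias but does not remove it: an arm-wide average of 55% against 50% still gives 1.10.

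The direction is also open. More selective prescribing, or early management that makes a course unnecessary, would lower the treated share and favour the intervention.

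The article already separates the two grades, so no redefinition is needed. That is true, and it makes the remedy cheap. Admission is itself partly a care decision, so the hospitalised version is not free of behaviour either.

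Three stronger readings are tempting, and the document does not support them:

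- A reader might infer that any antibiotic course counts, whatever the indication. The item is headed as exacerbations and the brackets grade their severity. How a course is tied to a respiratory episode is an extraction rule that a condensed article may leave to the full protocol.
- A reader might infer that courses issued in advance under an action plan count even if unused. The article mentions no such supply.
- A reader might infer unmasked extraction of exacerbations. Item 3b does not say who extracts them, and silence on masking in a condensed article is not a finding.

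**Conclusion.** The point holds as a limited one. As fixed in the article, the moderate count can pick up treatment behaviour as well as disease. The ratio built on exacerbations prevented does not say which grades it uses, so a reader could not tell which of the two drives it.

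Neither the size nor the direction of the bias can be derived from the document. The figures above rest wholly on assumed treated shares and show only that moderate differences in behaviour would be enough to matter. A reader might conclude that the endpoint must count against the intervention; the text does not establish that.

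The consequence is confined to the moderate component of one secondary outcome and one of five ratios. The CCQ primary outcome and costs per QALY are not affected through this count.

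**What to change.** 1. State which grades enter the costs per exacerbation prevented.
2. Report moderate and hospitalised exacerbations separately by arm, and describe the moderate component as treated episodes.
3. Calculate the ratio twice: for hospitalised exacerbations alone, and for moderate plus severe. Draw a conclusion on exacerbations prevented only if the two versions agree in direction.

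Two further rules may suggest themselves: leaving out courses started under an action plan, or counting a course only when a contact is recorded beside it. Neither is advised. The intervention supports recording, and an episode treated at home may leave no contact, so either rule could create a new difference between arms.

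The grades are already separated in item 3b, so the change costs only a little extra analysis. The hospitalised version will have fewer events and a wider interval, and it remains partly dependent on admission decisions.
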